## Discussion

### Principal Findings

This study aims to find potential predictive and prognostic biomarkers in patients with MF and SS. This study will investigate translational samples from skin and blood concerning the stage of the disease over time, which has the advantage of monitoring patients with consecutive samplings to be able to capture changes before and during a possible progression. This study will be able to compare differences in patients with early (IA-IIA) and advanced (IIB-IVB) stages of the disease. It will also be possible to analyze the data separately for patients with MF and SS, respectively. The translational samplings in this study are chosen to be able to detect changes in the immune system and in tumor cells, as well as changes in the skin barrier function and the skin microbiota. There is a clinically unmet need to find new predictive and prognostic biomarkers in MF and SS, and studies further exploring these areas are therefore a high priority. The research team, techniques, and management presented in this protocol have capacities to investigate new aspects and bring new knowledge to the field of CTCL. This study combines a multidisciplinary outpatient clinic with extensive translational research sampling, which has considerable potential to lead to true patient benefit.

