## Introduction

### Mycosis Fungoides and Sézary Syndrome

Cutaneous T-cell lymphoma (CTCL) is a rare group of lymphomas that primarily affects the skin [1-3]. The pathogenesis of CTCL is not yet fully understood [3]. The annual incidence of CTCL is 0.7 per 100,000. Mycosis fungoides (MF) is the most prevalent form and comprises 60% of CTCL, with a higher male incidence (1.6:1.0) and a peak age incidence between 50 and 74 years [4]. Since MF often has a chronic course, its prevalence is considerably higher. The skin lesions in MF can be patches, plaques, tumors, or erythroderma. Sézary syndrome (SS) is an aggressive leukemic variant of the disease and constitutes only 5% of CTCL; it is defined as a triad of erythroderma, lymphadenopathy, and the presence of neoplastic T-cells in peripheral blood [5]. The extent of the disease in the skin is measured according to the Modified Severity-Weighted Assessment Tool [6,7]. Both MF and SS are staged according to the same tumor-node-metastasis-blood (TNMB) classification, assessing the involvement of skin, peripheral lymph nodes, peripheral blood, and visceral organs [8].

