## Methods

### Study Design

The Predictive and Prognostic Biomarkers in Patients With MF and SS (BIO-MUSE) study is a translational prospective study, aiming to include 120 adult patients with MF and SS and a control group of 20 healthy volunteers (Figure 1). Sampling of each patient will be performed every 3 months for 3 years. The control group will be examined on 3 different occasions at least 2 months apart. This study is presently open at Skåne University Hospital and aims to open at Karolinska University Hospital. The multicenter study design enables other Swedish sites to be included, after further ethical approval.

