## Results

Patient inclusion started in 2021 and is still ongoing in December 2023, with 18 patients and 20 healthy controls enrolled. Until December 2023, a total of 2 included patients have declined further participation due to the extra visits in this study. Further, 2 patients have died from MF during this study. The publication of selected translational findings before the publication of the main results of the trial is accepted, and data analysis is in progress.

The evaluation of the stage of the disease will be observed every 3 months according to the TNMB classification, where the shift from one stage to another implies progression or treatment response. After the study, patients will be grouped as either early stage of the disease (IA-IIA) or advanced stage of the disease (IIB-IVB). The patients crossing over from the early stage of the disease to the advanced stage of the disease group will be analyzed both individually and as a group. Approximately 30% (36/120) of patients are estimated to be in the advanced stage of the disease group. The translational samples in the early stage of the disease group will be compared to samples from the advanced stage of the disease group. The treatments directed against MF are documented throughout this study. Excluded patients will be presented along with the final results. Depending on patient numbers, treatment data will be presented descriptively, or if possible, to support data on treatment predictive biomarkers.

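### About 9 of 120 patients would be expected to have SS, enough for description but not marker inference, and comparing blood T-cells by TNMB stage partly reflects how the stages are defined

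*Protocol article*

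**What the plan says.** **Size of the SS group.** In the Introduction (Mycosis Fungoides and Sézary Syndrome) the article says "Mycosis fungoides (MF) is the most prevalent form and comprises 60% of CTCL", and that SS "constitutes only 5% of CTCL". Study Design describes one cohort, "aiming to include 120 adult patients with MF and SS", and the article gives no quota, minimum or expected number for SS. Principal Findings then says: "It will also be possible to analyze the data separately for patients with MF and SS, respectively". No condition is attached. By contrast, the Results section makes the use of treatment data for predictive markers depend on how many patients there are.

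**Stage and blood.** MF and SS share one staging system, TNMB, described as "assessing the involvement of skin, peripheral lymph nodes, peripheral blood, and visceral organs". SS itself is partly defined by neoplastic T-cells in blood. The section on lymphocyte subpopulations plans two flow-cytometry antibody sets in blood, one for T-cell subsets and one for clonal T-cells. Statistical Analysis compares stages IA-IIA with IIB-IVB by principal components and the Mann-Whitney test, and Results repeats this: "The translational samples in the early stage of the disease group will be compared to samples from the advanced stage of the disease group". Under Goals of This Study, the blood immune-cell profile is one of two parts of the primary objective, which is framed in terms of 6-month progression-free survival (PFS).

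**The concern.** There are two linked issues.

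First, a reader of the Discussion would expect usable SS-specific results. If the cohort holds only about nine SS patients, any marker claim within SS would rest on a handful of progressors, tested across many proteins and cell subsets.

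Second, a blood T-cell measurement is compared between groups that are themselves formed partly from blood findings. A minority of patients with blood involvement could then produce an apparent stage marker, even if the rest of the advanced group looks like early disease. At stake is whether a reported difference in the blood immune-cell profile tells the reader anything beyond the blood component of the stage already assigned.

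**Working it through.** **Inputs from the article.** 120 patients; MF 60% and SS 5% of CTCL; about 30% advanced. **My assumptions.** Two-sided alpha 0.05 and 80% power (neither is stated); for the simulation, that all SS patients fall in the advanced group (inferred from the SS definition, not stated).

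**1. The plan's own figure.** 0.30 × 120 = 36 advanced patients, as stated, leaving 84 early.

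**2. Expected SS count.** The SS share among MF plus SS is 5/(60 + 5) = 7.7%, and 120 × 0.077 = 9.2. The binomial 2.5% to 97.5% range for n = 120 is 4 to 15. About 111 patients would have MF. Nine SS patients would be 9.2/36 = 26% of the advanced group.

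The shares describe CTCL as a whole, not the enrolled mix. The article adds "Since MF often has a chronic course, its prevalence is considerably higher", which would lower the SS share among prevalent patients. Recruitment through university hospitals could raise it. Taking 5% directly gives 6 patients; assumed shares of 10%, 15% and 20% give 12, 18 and 24.

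**3. What nine patients can show.**
- Precision: 4 of 9 progression-free has an exact 95% interval of 14% to 79%.
- Smallest possible two-sided exact Mann-Whitney p when nine patients are split by 6-month PFS, 2/C(9,k): 2 vs 7 gives 2/36 = 0.056; 3 vs 6 gives 2/84 = 0.024; 4 vs 5 gives 2/126 = 0.016. All are before any multiplicity adjustment.
- Detectable difference, (1.96 + 0.84) × √[(1/a + 1/b)/(3/π)]: 4 vs 5 gives 1.9 SD and 3 vs 6 gives 2.0 SD. For comparison, SS vs MF (9 vs 111) gives 1.0 SD, and advanced vs early (36 vs 84) gives 0.57 SD.

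**4. How far blood involvement alone can create a stage difference.** I simulated a normally distributed blood marker in 84 early and 36 advanced patients (2,000 runs per setting). Only the SS patients were shifted; the other advanced patients had the same distribution as early disease. Mann-Whitney rejection rates at 0.05:

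| Shift in SS | 4 SS | 9 SS | 12 SS |
|---|---|---|---|
| 0 SD | 5% | 6% | 5% |
| 1 SD | 7% | 18% | 31% |
| 2 SD | 12% | 44% | 71% |
| 3 SD | 13% | 57% | 84% |

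With nine SS patients the mean AUC is 0.61 at 2 SD and 0.62 at 3 SD. The rejections are not errors in the formal sense, because the two distributions do differ. But they come entirely from a quarter of the advanced group. SS stands in here for blood involvement in general; MF patients with blood involvement would add to the effect, but the article gives no count for them.

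**The case against.** The strongest reply on SS is that the sentence in Principal Findings promises little. It names no test, endpoint or power, and a separate SS analysis appears neither in the objectives nor under Statistical Analysis. About 111 MF patients can be analysed on their own, SS can be described, and a large SS-versus-MF difference could be seen. All of this stands. A reader might infer that a separate SS analysis is impossible; the documents do not support that. They leave the sentence unqualified where a qualification is needed.

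On stage, a reader might infer that the comparison is circular and would simply return the staging definition. That is too strong. On the article's shares about 27 of the 36 advanced patients would not have SS, and the rejection rates above are well short of certainty. The overlap is close to complete only for markers of clonality or blood tumour burden. It is partial for subset proportions, and does not apply in the same way to serum proteins, immunoglobulin E, skin or barrier measurements. Nor is SS the sole cause: blood is a staging component for MF too, so removing SS would not remove the overlap.

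It can also be said that the primary objective concerns 6-month PFS rather than stage, and that the article plans to examine patients who cross from early to advanced disease. Both are true. The overlap bears on the stage comparison that the article describes, and on the primary objective only so far as that comparison is used to serve it.

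Finally, sensitivity analyses are often left to an analysis plan that is not shown here. That limits the point to what the article itself fixes: the grouping and the unconditional sentence.

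**Conclusion.** The point holds in a limited form. On the article's own shares the expected SS group is about 9 of 120 (4 to 15 by chance alone, wider once referral and prevalence are allowed for). That number supports description. Within SS, only marker differences of about 2 SD would be detectable with 80% power, and some splits cannot reach 0.05 at all.

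The early-versus-advanced comparison of blood T-cells carries partial incorporation bias, because TNMB stage includes blood. Its possible size is illustrated by the 44% to 57% rejection when nine patients are shifted by 2 to 3 SD and nobody else differs. Those figures assume that all SS counts as advanced and that the shift is of that size; the article gives neither. With four SS patients the rate is only 12% to 13%, so the effect depends heavily on how many patients have blood involvement.

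**What to change.** - **Principal Findings:** state the expected SS count with its range, and say that SS results will be descriptive and depend on patient numbers.
- **Statistical Analysis and Results:** keep the all-patient stage comparison of the blood immune-cell profile. Add a prespecified comparison restricted to patients without blood involvement (and without SS), or one adjusted for blood class, or both.
- **Interpretation:** do not present clonal T-cell markers that differ by stage as new stage findings.

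One remedy that may suggest itself does not work with the panels as listed: removing clonal cells by TRBC1 and re-expressing the subsets among the remaining T-cells. The subset antibodies and the TRBC1 panel are listed separately and share only CD4 and CD8, so the naive, memory, helper and regulatory subsets could not be recovered among non-clonal cells by re-gating.

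The cost is some wording and a little more analysis of data already planned. The added comparison has a smaller advanced group. Dropping nine SS patients alone (27 vs 84) raises the detectable difference from 0.57 to 0.63 SD, and excluding MF patients with blood involvement would raise it further by an amount the article does not allow one to calculate. This is a reason to add the comparison rather than put it in place of the all-patient one.

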### Limitations

MF and SS are rare diseases, and the inclusion of the proposed number of patients in this study protocol may take considerable time. To reach the estimated number of patients in this study, inclusion will also start at Karolinska University Hospital, and to expand this study further, cooperations with other centers is ongoing. Another possible limitation is that the control group will be followed for a shorter period compared to the patients.

### Comparison With Prior Work

The Prospective Cutaneous Lymphoma International Prognostic Index study is an ongoing international study of a confirmed early-stage MF cohort, which is being followed up to identify prognostic factors in the hope of providing better management and improving survival by identifying patients at risk of disease progression [36].

### Conclusions

The BIO-MUSE study is a prospective translational study aiming to identify new prognostic and predictive biomarkers in blood and skin in patients with MF and SS.

## Appendix

Multimedia Appendix 1 Translational samples and logistics for patients in the Predictive and Prognostic Biomarkers in Patients With Mycosis Fungoides and Sézary Syndrome (BIO-MUSE) study.

Multimedia Appendix 2 Translational samples and logistics for the healthy control group in the Predictive and Prognostic Biomarkers in Patients With Mycosis Fungoides and Sézary Syndrome (BIO-MUSE) study.

Multimedia Appendix 3 Planned assessments of hematopathology in the skin, lymph node, bone marrow, and tumor biopsies.

## Abbreviations

ATAC-seq: assay of transposase-accessible chromatin with sequencing
BIO-MUSE: Predictive and Prognostic Biomarkers in Patients With Mycosis Fungoides and Sézary Syndrome
CBC: complete blood count
ChIP-seq: chromatin immunoprecipitation with sequencing
CTCL: cutaneous T-cell lymphoma
HDAC: histone deacetylase
MF: mycosis fungoides
PFS: progression-free survival
SDT: skin-directed therapy
SS: Sézary syndrome
TEWL: transepidermal water loss
TNMB: tumor-node-metastasis-blood
